## Abstract

**Background:**

Excessive alcohol consumption amongst university students has received increasing attention. A social norms approach to reducing drinking behaviours has met with some success in the USA. Such an approach is based on the assumption that student's perceptions of the norms of their peers are highly influential, but that these perceptions are often incorrect. Social norms interventions therefore aim to correct these inaccurate perceptions, and in turn, to change behaviours. However, UK studies are scarce and it is increasingly recognised that social norm interventions need to be supported by socio ecological approaches that address the wider determinants of behaviour.

**Objectives:**

To describe the research design for an exploratory trial examining the acceptability, hypothesised process of change and implementation of a social norm marketing campaign designed to correct misperceptions of normative alcohol use and reduce levels of misuse, implemented alongside a university wide alcohol harm reduction toolkit. It also assesses the feasibility of a potential large scale effectiveness trial by providing key trial design parameters including randomisation, recruitment and retention, contamination, data collection methods, outcome measures and intracluster correlations.

**Methods/design:**

The study adopts an exploratory cluster randomised controlled trial design with halls of residence as the unit of allocation, and a nested mixed methods process evaluation. Four Welsh (UK) universities participated in the study, with residence hall managers consenting to implementation of the trial in 50 university owned campus based halls of residence. Consenting halls were randomised to either a phased multi channel social norm marketing campaign addressing normative discrepancies (n = 25 intervention) or normal practice (n = 25 control). The primary outcome is alcohol consumption (units per week) measured using the Daily Drinking Questionnaire. Secondary outcomes assess frequency of alcohol consumption, higher risk drinking, alcohol related problems and change in perceptions of alcohol-related descriptive and injunctive norms. Data will be collected for all 50 halls at 4 months follow up through a cross-sectional on line and postal survey of approximately 4000 first year students. The process evaluation will explore the acceptability and implementation of the social norms intervention and toolkit and hypothesised process of change including awareness, receptivity and normative changes.

**Discussion:**

Exploratory trials such as this are essential to inform future definitive trials by providing crucial methodological parameters and guidance on designing and implementing optimum interventions.

**Trial registration number:**

ISRCTN: ISRCTN48556384

## Background

Excessive alcohol consumption among university students has been linked to a range of adverse outcomes, including educational difficulties, psychosocial problems, antisocial behaviours, injuries, risky sexual behaviours and drink driving [1]. In the United Kingdom, alcohol consumption levels amongst university aged adults increased rapidly during the 1990s [2]. Recent studies suggest that just over half of UK university students 'binge drink' (i.e. consume 5 or more drinks in one sitting) at least once per week [3,4], whilst as many as 80% binge drink at least once a month [4]. One recent study estimated average alcohol consumption at 25 units per week for 1^st ^year male UK undergraduates and 16 for 1st year women [5], significantly above current public health recommendations. Recent UK government policy of increasing the percentage of young people going to university has perhaps had the effect of exposing a larger proportion of the population to this high-risk drinking environment.

Alcohol consumption amongst university students has to date proved highly resistant to intervention efforts [6]. One approach, which has shown some promise in experimental studies, is addressing the perceived social norms that are posited to influence alcohol consumption [7]. Perceived norms take the form of descriptive norms, with behaviour modelled through observation of the behaviour of significant others; or injunctive norms, where the individual perceives that their peers expect them to behave a certain way. Interventions underpinned by the social norms approach argue that normative perceptions are highly fallible, with students often overestimating real alcohol consumption patterns among peers [8]. Hence, through providing feedback and correcting misperceptions regarding the behaviours and social expectations of peers, alcohol drinking behaviours may be reduced. Social norms interventions have typically involved provision of mailed, web-based or face-to-face feedback on individual's drinking behaviour and how this compares to norms for their peer group, or social marketing campaigns to promote awareness of actual norms. A recent Cochrane review concluded that feedback-based interventions delivered via the internet or face-to-face on a one-to-one basis appeared to reduce student drinking behaviours, though mailed or group feedback were less effective, and findings for social marketing campaigns were equivocal [7].

Whilst demonstrating promise, such interventions have typically been examined in isolation from the contexts in which they operate and significant questions remain to be addressed regarding how they might be applied in practice. No such studies have taken place in Wales, with the limited number of UK based studies suffering substantial weaknesses such as high levels of attrition [9]. Furthermore, universities are complex systems, whose overall ethos, policies and practices may provide a context supportive of change, or of maintaining the status quo [10]. Interventions which aim to achieve long-term change through simply targeting cognitive factors such as normative perceptions, without addressing the characteristics of the setting which support the status quo are likely to fail in the longer term [11]. Some community-based interventions to reduce alcohol consumption in adolescents have for example been shown to be more effective in rural settings than urban settings, where impacts of the intervention are perhaps drowned out by the multitude of pro-alcohol stimuli in the urban environment [12]. In Welsh universities, university managed accommodation blocks (halls of residence) primarily house students in their first year of attendance, with approximately half of students living in halls during their first year. Given that first year students are at greatest risk of excessive alcohol consumption [5], halls of residence offer potential as a means of reaching those students most at risk for alcohol related intervention.

The proposed research therefore aims to assess the value of a social marketing-led social norms-based intervention implemented in University halls of residence across four Universities in Wales. A survey of first year students was conducted in participating universities in May 2011, in order to establish levels of drinking and the prevalence of alcohol related consequences, as well as normative perceptions. Findings from the survey fed into the development of materials by an Intervention Steering Group to communicate areas of normative misperception (e.g. the extent to which students overestimated peer drinking volume), to be distributed within halls of residence. All halls of residence participating in the study will experience a university-wide alcohol harm reduction toolkit, with half randomised to additionally receive the social norms intervention.

An exploratory cluster randomised design with nested process evaluation will be used to identify appropriate outcome measures and data collection methods, test randomisation processes, assess the extent of contamination across trial arms and establish recruitment and retention rates and intra-cluster correlations to help inform sample size for any future definitive trial. It will also identify whether the intervention effectively mobilises the underpinning theory and that this is sufficient to bring about hypothesised responses in terms of awareness, engagement and changed perception of norms. Whilst intervention acceptability and implementation processes will be assessed within the process evaluation.

## Methods/design

### Research design

Figure 1 provides a summary of the study; an exploratory cluster randomised controlled trial design with nested mixed methods process evaluation. Ethical approval was provided by Cardiff University, School of Social Sciences Research Ethics Committee, with separate applications approved for the process evaluation (SREC/752) and the cluster randomised trial (SREC/857)

**Figure 1 F1:**
[figure not shown]
**Research design**.

### The intervention

The intervention is a social norm marketing campaign, which aims to correct misperceptions regarding the behaviours and social expectations of peers and in so doing influence alcohol consumption. The campaign will be delivered in two phases between October 2011 and May 2012 in intervention halls of residence in four universities and will use a variety of materials encompassing posters, beer mats/coasters, leaflets, meal planners and drinking glasses. The campaign will be implemented by university accommodation staff. Social norm messages were based on the results of a survey of first year university students conducted in study universities in late April/May 2011 which identified discrepancies between norms and behaviours. Table 1 highlights the intervention materials and main social norm messages within them.

**Table 1 T1:** Social norms intervention components and examples of core messages communicated within them

Timing	Material	Core message
October 2011	Posters	'Those around you are drinking less than you think: students overestimate what others drink by 44%' 'Most of us significantly overestimate the amount that others drink'
	
	Beer mats/coasters	'Those around you are drinking less than you think: students overestimate what others drink by 44%' 'Most of us significantly overestimate the amount that others drink'
	
	Window stickers	'Few of us approve of people who drink to the point of losing it'

January 2012	Posters	'Most students drink to feel confident, but 70% have embarrassed themselves when drunk'
	
	Drinking glasses	'Time for a break? Many students limit their drinking by including soft drinks in the night'
	
	Gender specific leaflets	Males: '86% of Males have never damaged their halls of residence when drunk' Females: 'How much do you think the average female first year student drinks? Halve it. It really is less than you think.'

Universities in the study also receive a toolkit to promote institutional responsibility for prevention, audit current alcohol misuse policies and practices and which provided advice and guidance on prevention. The toolkit was developed by a National Union of Students (NUS) intervention project officer in consultation with the universities in the study. It was distributed to key university stakeholders in October 2011 with the intention of developing a supportive environment for the intervention. Control halls will be exposed to the toolkit only. The toolkit and social norms intervention were developed collaboratively by Drinkaware, NUS Wales and the Welsh Government following a review of previous interventions and support from an academic supervisor. Their implementation was facilitated by a dedicated NUS project officer. Given the nature of the intervention, it was not possible to blind participants to condition.

### Recruitment

Six universities who had collaborated on the development of the intervention were approached by the evaluation team to participate in the study, with four agreeing to implement the intervention in the study period. Reasons for non-participation were related to difficulties in implementing the intervention and obtaining university consent within the evaluation timeframe. Informed consent for the study was obtained from directors of student services and halls of residence managers. The universities varied in terms of the number of full-time first year students (from 1100 to 3327), and location, with a mixture of urban and rural locations.

### Inclusion/exclusion criteria

The four universities had a total of 51 on campus university owned halls of residence. One female only hall was excluded due to lack of trial arm balance. All remaining halls (n = 50) were eligible for inclusion and consented to randomisation, although 5 halls in one site were empty during the first phase of the campaign due to renovation.

### Randomisation

Blind remote randomisation was used to allocate halls of residence to receive the social norms plus toolkit intervention or toolkit only. Halls were stratified by institution and halls allocated alternately in a list ordered by size, with the group allocation determined by one random number within each stratum.

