### Sample size

Assuming a student response rate of 40%, 1600 completed questionnaires will be available for analysis, an average of 32 students per hall. Assuming an intra-cluster correlation of 0.03, fifty halls of residence will therefore provide 80% power to detect a 0.2 standard deviation difference in units of alcohol consumed using a two-tailed alpha of 0.05.

Assuming a student response rate of 25%, 1000 completed questionnaires will be available for analysis, an average of 20 students per hall. Assuming an intra-cluster correlation of 0.03, fifty halls of residence will therefore provide 80% power to detect a 0.23 standard deviation difference in units of alcohol consumed using a two-tailed alpha of 0.05.

It is not anticipated that the effect size will be of this magnitude, with a much larger trial likely to be necessary to detect realistic effect sizes below 0.1 standard deviation. This study is therefore designed as an exploratory trial to assess the value of the intervention and plan a larger scale study if warranted.

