### Analysis

In order to assess exposure to intervention materials and contamination between trial arms, percentages of students within the intervention and control groups reporting having seen each of the intervention materials i) in their own hall of residence and ii) in another students' hall of residence will be examined. Among those students reporting exposure to intervention materials, percentages correctly identifying the messages within them will be calculated for each trial arm. Percentages of students reporting each level of agreement with statements regarding the credibility, relevance and perceived impacts of intervention materials will also be examined for each trial arm.

Whilst the study is likely not sufficiently powered to detect impacts on behaviour, it is likely that relatively large changes in perceived norms will be necessary to produce small changes in behaviour. Hence, regression analyses, with random terms to adjust for clustering at the hall level, and fixed terms to adjust for stratification variables, will examine differences between intervention and control participants in terms of normative perceptions for alcohol consumption and alcohol related consequences. Comparisons between trial arms will be conducted on an intention-to-treat basis. Secondary analyses would compare halls on the basis of researcher observations of whether or not materials were placed.

To inform the design of a potential large scale definitive trial with sufficient power to detect changes in behaviour, intra-cluster correlations and standard deviations will be calculated for total number of units per week. Response rates will be calculated in each trial arm. The percentage of students reporting willingness to provide hair samples will also be presented, whilst among those students reporting that they would only do so if paid, percentages reporting that each level of payment would be required would be presented.

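### Hall size restricted the allocation but is not stated to be a model term; naming it costs nothing and protects precision

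*Protocol article*

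**What the plan says.** The Randomisation section of the protocol article gives the allocation rule in two parts. First, "Halls were stratified by institution". Second, within each institution there were "halls allocated alternately in a list ordered by size, with the group allocation determined by one random number within each stratum". The Abstract reports that "Four Welsh (UK) universities participated in the study", and the inclusion criteria add that "All remaining halls (n = 50) were eligible for inclusion and consented to randomisation". The Abstract also reports 25 halls in each arm.

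The Analysis section plans regressions with a random term for hall and "fixed terms to adjust for stratification variables". It does not list those variables. Hall size is not mentioned in that section, either as included or as excluded.

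The Background lists among the aims of the study to "test randomisation processes".

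**The concern.** Two variables restricted the allocation: institution, as the stratifier, and hall size, as the ordering of the list. Only the first is called a stratification variable. Read literally, the model adjusts for institution and leaves out size.

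When a design balances a variable and the analysis ignores it, the treatment estimate varies less than the model assumes. If that variable is related to the outcome, the reported standard error is too large, the test is conservative and power is lost. The planned regressions are the means of detecting changes in perceived norms, and the article already says that power for behaviour is limited, so avoidable imprecision matters here.

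A smaller matter is transparency. Testing the randomisation process is a stated aim, and this scheme has far fewer possible outcomes than 50 randomised halls might suggest.

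**Working it through.** **Inputs from the protocol article.** 4 institutions, 50 halls (25 and 25), one random number per institution. Intra-cluster correlation (ICC) 0.03, two-sided alpha 0.05. At 40% response, "1600 completed questionnaires will be available for analysis, an average of 32 students per hall", with 0.2 SD detectable at 80% power. At 25% response, 20 per hall, with 0.23 SD detectable at 80% power.

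**Assumptions, because the articles gives no figures.** Halls per institution, the spread of hall sizes, and the hall-level correlation ρ between size and outcome. About 4000 students in 50 halls gives a mean of 4000/50 = 80 per hall.

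**1. The plan's own power.** Variance of a hall mean in SD units: v = ICC + (1 − ICC)/m. Standard error of the arm difference: √(4v/50). Power from the noncentral t.
- m = 32: v = 0.03 + 0.97/32 = 0.0603; SE = 0.0695; 0.2/0.0695 = 2.88; power 80.5% on 48 df.
- m = 20: v = 0.03 + 0.97/20 = 0.0785; SE = 0.0793; 0.23/0.0793 = 2.90; power 81.2% on 48 df.

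Both stated figures are reproduced.

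**2. What size in the model could recover.** If size explains a share ρ² of the between-hall variance, v becomes ICC(1 − ρ²) + (1 − ICC)/m. Degrees of freedom are 50 − 5 = 45 without size and 44 with it.

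| | Without size | With size, ρ = 0 | With size, ρ = 0.5 | With size, ρ = 0.9 |
|---|---|---|---|---|
| m = 32: v | 0.0603 | 0.0603 | 0.0225 + 0.0303 = 0.0528 | 0.0057 + 0.0303 = 0.0360 |
| SE | 0.0695 | 0.0695 | 0.0650 | 0.0537 |
| Power, 0.2 SD | 80.4% | 80.4% | 85.3% | 95.4% |
| m = 20: v | 0.0785 | 0.0785 | 0.0710 | 0.0542 |
| Power, 0.23 SD | 81.1% | 81.0% | 84.7% | 92.7% |

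This closed form takes halls of equal size and treats size as balanced between arms, so it is an approximation.

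**3. Simulation under no effect.** 3000 runs per setting; strata of 12/12/12/14 or 6/8/12/24 halls; mean size 80; coefficient of variation (CV) of size 0.3 or 0.6; ICC 0.03; weighted hall-level regression with institution terms; alternation as described.
- Type I error without size: 4.8–5.3% (ρ = 0), 3.6–4.6% (ρ = 0.5), 2.3–2.8% (ρ = 0.9).
- With size: 4.2–5.8% across all settings.
- Average bias was about zero throughout.

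One setting shows the mechanism. With strata 12/12/12/14, CV 0.3 and ρ = 0.9, the unadjusted estimate had a standard deviation of 0.062 under alternation, against 0.071 under random allocation within institution. A model without size does not credit that gain.

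**4. Simulated power for 0.2 SD (CV 0.6).** Adding size raised power from about 80–82% to 84–85% at ρ = 0.5, and from about 83–84% to 94–96% at ρ = 0.9. If respondents are set at 40% of each hall's size (lognormal sizes, 4000 runs), the levels are lower but the pattern is the same: about 77% to 82%, and about 78% to 93%. At ρ = 0 the loss was about one point at most.

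**5. Balance on size.** Mean absolute difference in mean hall size between arms, alternation against random allocation within institution: 3.2–3.4 against 5.4–5.5 residents (CV 0.3), and 6.8–7.2 against 10.7–10.9 (CV 0.6).

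**6. Number of allocations.** One binary start in each of 4 institutions gives 2⁴ = 16. This is an upper bound: if two or four institutions have an odd number of halls, only 8 or 6 of the 16 give the reported 25:25 split.

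**The case against.** Several objections have force.

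- **The text may already include size.** The Analysis section speaks of variables in the plural and does not name them. Size restricted the allocation, so it may be meant. A condensed article can also leave a covariate list to the analysis plan, which is not at hand. This stands: one cannot say that size is excluded, only that it is not stated to be included.
- **A reader might infer that tying size to arm confounds the comparison.** The documents do not support that. Each hall had a 50% chance of either arm, and alternation balances size better than simple randomisation within institution. Nor is one arm bound to have larger halls on average. In an institution with an odd number of halls, the arm that takes the larger hall of each pair also takes the unpaired smallest one. For example, sizes 5, 4, 3, 2, 1 split into 5, 3, 1 and 4, 2, both with mean 3.
- **A reader might infer that 16 allocations invalidate a 5% test.** An exact re-randomisation test could not go below 2/16 = 0.125, but none is planned. The planned inference is a mixed regression, and the simulated type I error was nominal or conservative.
- **The trial is exploratory and its method is openly described.** True, and this limits the importance of the point. It does not remove the gain from one added term.

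**Conclusion.** The point holds as a matter of precision and clarity, not of bias. The article describes hall size as restricting the allocation and does not state that it enters the model. If size is prognostic, omission makes the test conservative and wastes power. The closed-form loss at 0.2 SD and 32 per hall is about 5 points at ρ = 0.5 (85.3 − 80.4) and 15 points at ρ = 0.9 (95.4 − 80.4). Simulated losses are about 3 to 5 and 11 to 15 points. At ρ = 0 nothing of note is lost.

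These sizes rest on assumed correlations, hall-size spread and halls per institution. A correlation of 0.9 is an extreme case, shown to mark the upper end. The effect shown is a loss of precision, not a false-positive risk, so this is a free improvement rather than a defect that threatens the trial's conclusions. The limit of 16 allocations is a minor reporting point.

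**What to change.** In the Analysis section, replace the general reference to stratification variables with a named list: institution and hall size (for example the log of the number of residents), both as fixed terms in every between-arm model. This costs one degree of freedom (45 to 44 at hall level). It needs no new data, because the halls were already ordered by size, and it leaves the allocation unchanged.

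When the randomisation process is reported, add one sentence saying that halls were allocated systematically from one random start per institution, which allows at most 16 allocations. This costs only the wording.
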